### Follow-up (visits/assessments/measures/tools)

Follow-up (Fig. 1) by the RO occurs via phone at day 3 and weekly from weeks 1–3 and 5–11 and at Aboriginal Health Services at 1, 3, and 6 months post-enrolment and randomisation (day 0). Data sources, the findings of which are recorded on trial-designed paper source document worksheets, include tympanometry, video pneumatic otoscopy, audiometry, adherence and cost-effectiveness progress questions, an OMQ-14 quality of life questionnaire [35], nasal autoinflation adherence diary, and qualitative interviews. Medically trained CIs review participant medical records for additional information related to ear disease and treatment including adverse events, health care utilisation, and medication usage, for up to 6 months post-randomisation. This information informs determination of secondary outcomes including the cost-effectiveness analysis. Details of data collection at each of the scheduled assessment times are summarised in Table 1.

**Fig. 1 Fig1:**
[figure not shown]
Recruitment flowchart

**Table 1 Tab1:**
[figure not shown]
Enrolment/intervention/assessments

This trial does not include collection of biological specimens for current or future use.

### Study completion/withdrawal/lost to follow-up

Study completion is defined as a completion of 1- and 6-month assessments at minimum. Participants may withdraw or be withdrawn from the trial by a parent/carer, treating physician, or CIs at any stage of follow-up. The independent DSMB may also recommend participant withdrawal from the trial in the event of a significant safety issue. Reasons for and the extent of withdrawal (treatment only, treatment and trial assessments, or treatment, trial assessments, and data collection) are recorded. Participants who have not withdrawn and do not complete either their 1- or 6-month assessment are deemed lost to primary outcome or final status follow-up respectively.

### Data management

Source data is captured either in password-protected participant electronic medical record databases, on trial-designed paper source document worksheets, or diagnostic device paper or electronic software output. Paper source documents are stored in a lockable cabinet, and electronic source documents in password-protected health service databases, accessible to authorised health service staff only. Source data is de-identified and coded using randomisation number before it is single entered by the RO into an encrypted, password-protected validated electronic Case Report Form database (Medrio™) hosted in the USA. De-identified, coded data is accessible to authorised health service and WSU staff only. Qualitative interviews are taped and transcribed, then electronic copies de-identified and coded using randomisation number, for storing by WSU. Paper and electronic source data will be securely archived by health services, and de-identified, coded data, by WSU, for a minimum of 15 years after completion of the trial.

### Data monitoring

All data collected from the first patient recruited at each participating site are reviewed for accuracy and validity. Consent, eligibility, primary outcome data points, serious adverse events, and select adverse events of interest are monitored for all participants. All remaining data are randomly monitored (estimated 10% of participants) for quality assurance purposes.

INFLATE is a low-risk trial using the nasal autoinflation device within its marketed indication and population. Given the low-risk nature of the trial, the use of ongoing centralised statistical and on-site monitoring, and ongoing site and WSU staff training, an external audit will not be conducted.

### Sample size and power

It is estimated that a sample size of 340 children (170 in each treatment group) will detect an absolute difference of 15% between groups (relative difference relative risk = 1.43) in OME resolution rates at 1 month, with 80% power and a 5% significance level. The 15% difference represents a difference between an estimated 35% resolution in the control group and 50% resolution in the treatment group based on a similar trial [36]. This 15% absolute difference reduces the 65% non-resolution by approximately a quarter, which is clinically relevant. Assuming a 15% loss to follow-up, 400 children will need to be randomised. This sample size will also detect an effect size of 0.3 (assuming a standardised standard deviation = 1) for continuous secondary outcomes, such as OMQ-14 scores.

### Outcomes

#### Primary outcome

The proportion of children showing tympanometric improvement of OME at 1 month from baseline. Improvement is defined as a change from bilateral type B tympanograms to at least one type A or C1 tympanogram, or from unilateral type B tympanogram to type A or C1 tympanogram in the index ear, without deterioration (type A or C1 to type C2, C3, or B tympanogram) in the contralateral ear.

#### Secondary outcomes

The secondary outcomes are:
i)Proportion of children showing tympanometric improvement at 3 and 6 months from baseline (OME improved by child)ii)Proportion of ears showing tympanometric resolution of OME at 1, 3, and 6 months from baselineiii)Proportion of children showing tympanometric improvement at 1, 3, and 6 months from baseline (OME improved by child — unilateral and bilateral subgroups)iv)Proportion of tympanometric deterioration from a type A or C1 tympanogram to C2, C3, or B tympanogram in non-index ears at 1, 3, and 6 months from baseline (new OME by ear — unilateral subgroup)v)3-frequency average hearing levels (pure tone threshold audiometry) at 3 months from baselinevi)Ear-related health and quality of life score (using OMQ-14 quality of life questionnaire) at day 0 and months 3 and 6vii)Adverse events up to 6 months from baselineviii)Adherence to autoinflation from day 0 to month 1 (using paper adherence diary)ix)Medical and non-medical costs of OME and its treatmentx)Qualitative exploration of parent/carer and health care provider, AMS Research Officer and AMS reference group perspectives of otitis media, research processes and the research experience including the experience of using nasal balloon autoinflation

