**Table Taba:** 

**Tympanometry:** Best practice guidelines [2, 3] recommend pneumatic otoscopy and tympanometry for the diagnosis of OME. Tympanometry is a non-invasive test measuring tympanic membrane movement and middle ear air pressure — a proxy for determining the presence of middle ear effusion — and is depicted in graphical form (tympanogram). Tympanograms are classified as type A, B, C1, C2, or C3. Peaked type A and C1 tympanograms indicate the absence of effusion consistent with normal middle ears. A flat type B trace is diagnostic of middle ear effusion in the absence of pain and/or a bulging or perforated tympanic membrane. Type C2 and C3 peaked traces are characterised by significant negative middle ear pressure and are considered equivocal and cannot be used to either diagnose or exclude OME [4, 5].	

Acute otitis media (AOM) is a frequent reason for children to attend general practice and often results in the prescription of antibiotics [6, 7]. Resolution of AOM is often followed by a period of residual middle ear fluid, or OME. The prevalence of OME in Aboriginal and Torres Strait Islander children is disproportionately high, ranging from 10 to 30% [8, 9]. The risk factors are multifactorial including household crowding and poor functionality [10], exposure to tobacco smoke, food insecurity, child care attendance, older siblings, upper respiratory tract infection, family history, lack of breastfeeding [8], and socioeconomic disadvantage and other adverse social determinants of health arising as a consequence of ongoing colonisation [11, 12]. The duration and severity of disease, and the incidence of complications, are also higher among Aboriginal and Torres Strait Islander people, particularly in remote and rural regions of Australia [13, 14].

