### Study population/eligibility criteria

Aboriginal or Torres Strait Islander children, attending urban or regional Aboriginal Health Services, aged 3–16 years with unilateral or bilateral type B tympanograms are eligible for inclusion. Tympanometry is conducted by a trained research officer (RO), and eligibility, including trace type, is confirmed by the treating General Practitioner (GP). Exclusion criteria include clinical confirmation of a current acute upper respiratory infection, acute otitis media, perforated tympanic membrane, or ventilation tube in situ; ear surgery booked within 1 month of diagnosis; self-reported latex allergy, recent nosebleed (at least 1 nosebleed in last 3 weeks or > 1 nosebleeds in last 6 months); self-reported or documented history of an at-risk condition (e.g., immunosuppression); previous participation in the trial; or self-reported inability to use the autoinflation device (demonstrated by the inability to blow nose).

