### Treatment groups

The intervention group uses a nasal balloon autoinflation device, Otovent® [34], in both nostrils three times daily from baseline (day 0) for up to 3 months. Participants are instructed to temporarily cease autoinflation treatment while symptomatic for no more than 5 consecutive days in the event of an upper respiratory tract infection to minimise the potential for ear pain during autoinflation. Participants cease autoinflation at 1 month if they have bilateral type A, C1, C2, or C3 tympanograms. Those with a type B tympanogram in at least one ear are asked to continue autoinflation for a further 2 months. At 3 months, participants are advised to cease autoinflation irrespective of tympanogram results.

The control group is managed according to Australian treatment guidelines (usual care) and regular follow-up with ROs, without autoinflation. General Practitioners decide usual care taking into consideration a participant’s risk of more severe forms of OM.

Antibiotics, steroids, antihistamines, decongestants, and alternative therapies are not recommended use during trial participation. All children in the intervention and control groups undergo a hearing assessment by an audiologist at either the Aboriginal Health Service or an audiology service provider. Any participants with bilateral OME or hearing impairment at 3 months are reviewed by a GP for appropriate management, including referral for ENT assessment.

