#### Secondary outcomes

Generalised linear models will also be used to model secondary outcomes, with log-link function used for binary outcomes, identity link for continuous outcomes, and logarithm link for count outcomes. Secondary analyses will include per protocol and treatment received analyses. Missing data will be handled using multiple imputation, using multiple regression models approach. Separate ear-based analyses will be carried out using each ear as the unit of analysis, with generalised estimating equations (GEE) used to account for the correlation and clustering of ears within an individual. Resolution at the ear level will be deemed by a change from type B to type A or C1 at 1 month.

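### Tympanometric outcomes i–iv are scored by trace type alone, so a tube or perforation at follow-up can be labelled new OME or decide whether a child counts as improved

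*Protocol article*

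**What the plan says.** Under Outcomes, Primary outcome: "Improvement is defined as a change from bilateral type B tympanograms to at least one type A or C1 tympanogram", with a matching rule for unilateral disease that also requires no deterioration in the other ear. Under Outcomes, Secondary outcomes, items i and iii carry child-level improvement to 3 and 6 months ("Proportion of children showing tympanometric improvement at 3 and 6 months from baseline"), and no other definition of improvement is offered. Item ii is ear-level resolution at 1, 3 and 6 months. Statistical analyses, Secondary outcomes defines it as "Resolution at the ear level will be deemed by a change from type B to type A or C1 at 1 month". Item iv is "Proportion of tympanometric deterioration from a type A or C1 tympanogram to C2, C3, or B tympanogram in non-index ears" at the same three visits, and its label calls this new OME.

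Three other places bear on these rules:

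- The tympanometry box in the Introduction: "A flat type B trace is diagnostic of middle ear effusion in the absence of pain and/or a bulging or perforated tympanic membrane".
- Study population/eligibility criteria, which excludes at entry children with a "perforated tympanic membrane, or ventilation tube in situ; ear surgery booked within 1 month of diagnosis".
- Treatment groups: "Any participants with bilateral OME or hearing impairment at 3 months are reviewed by a GP for appropriate management, including referral for ENT assessment".

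The section on follow-up lists video pneumatic otoscopy among the data sources, and a medical-record review covering health care use up to 6 months. Neither enters the outcome definitions.

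**The concern.** The entry criteria ensure that a flat trace at baseline can be read as effusion. Nothing comparable is attached to the follow-up trace, although tubes and perforations can arise by then. The surgery exclusion looks only one month ahead, and the 3-month review can lead to ENT referral while tympanometric outcomes run on to 6 months.

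Two things follow. First, outcome iv can count an ear as new OME when the document's own reading of a flat trace does not support that. The same ear can turn a unilateral child whose index ear has cleared into a child not improved, through the no-deterioration clause. Second, operated children are not handled in one consistent way. A flat trace through an open tube scores as failure, while an A or C1 trace after the tube has blocked or come out scores as improvement. Review at 3 months is triggered by persisting disease or hearing impairment, so if autoinflation works, more control children would reach it. Whatever the scoring rule does to operated children would then fall unequally on the arms.

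**Working it through.** **The plan's own figure.** Sample size and power gives 35% v 50% at 1 month, 5% significance (taken as two-sided), 80% power. With pooled variance and no continuity correction:

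n = [1.960 × √(2 × 0.425 × 0.575) + 0.842 × √(0.35 × 0.65 + 0.50 × 0.50)]² / 0.15² = (1.370 + 0.582)² / 0.0225 ≈ 169.3, so 170 per arm.

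Power at 170 per arm is 80.2%, and 340 / 0.85 = 400. Both stated numbers reproduce. They concern the 1-month outcome only, so this point changes neither.

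**What the rule does with each ear at follow-up**

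| Ear | Trace | Score under the rule | Comment |
|---|---|---|---|
| Index ear, open tube | flat (B) | not improved | same as counting surgery as failure |
| Index ear, tube blocked or out | A or C1 | improved | surgery credited to the randomised arm |
| Non-index ear, perforation or open tube | flat (B) | new OME | the tympanometry box does not support the label |

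**Which visits are exposed.** Referral that follows the 3-month findings can affect only the 6-month results. The 3-month results are exposed only to surgery done before that visit.

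**Size, by assumption.** The documents give no surgery rate. Let p be the proportion improved without surgery, q the share of otherwise unimproved children who have surgery (equal in both arms), and suppose all of them then score A or C1. Each arm becomes p + q(1 − p), so the difference is

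[pT + q(1 − pT)] − [pC + q(1 − pC)] = (1 − q)(pT − pC).

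Borrowing 35% v 50% and 170 per arm as an illustration for a later visit:

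| q | Control | Autoinflation | Difference (points) | RR | Power |
|---|---|---|---|---|---|
| 0 | 35.0% | 50.0% | 15.0 | 1.43 | 80% |
| 5% | 38.25% | 52.5% | 14.3 | 1.37 | 75% |
| 10% | 41.5% | 55.0% | 13.5 | 1.33 | 70% |
| 20% | 48.0% | 60.0% | 12.0 | 1.25 | 60% |
| 30% | 54.5% | 65.0% | 10.5 | 1.19 | 51% |

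At q = 10%, about 11 control children (170 × 0.10 × 0.65) and 8 to 9 autoinflation children (170 × 0.10 × 0.50) are affected. If every operated child instead traced flat and scored not improved, the difference would stay at 15 points for any q. A mixture of the two lies in between.

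**The case against.** The strongest reply is that this is a condensed article. The handling of surgery and of traces that cannot be read is often left to the full protocol or the analysis plan, and the tympanometry box is background on diagnosis. Outcome iv is also worded as a shift in trace and includes C2 and C3, which the box calls equivocal. This has force for the choice of strategy for surgery, so its absence alone is not the point. What remains is that the article does state a scoring rule, attaches an OME label to it, and elsewhere gives a condition under which that label fails.

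Several stronger readings are tempting, and the documents do not support them:

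- **That including surgery is an error.** The trial is described as pragmatic and the primary analysis is by intention to treat, so a treatment-policy effect is legitimate. Making surgery-as-failure the sole definition would be a trade-off: it ties a trace-based outcome to referral decisions made with allocation known.
- **That operated ears are always scored wrongly.** A flat trace in an operated index ear already scores as surgery-as-failure would score it.
- **That hearing and OMQ-14 (items v and vi) share the defect.** Surgery may influence them, but they are not scored by trace.
- **That surgery is planned from month 1.** This can only be inferred from the exclusion window. The Introduction describes tube insertion as deferred to at least 3 months, and the 3-month trigger is a GP review that may include ENT referral, not surgery itself.
- **That surgery could erase the effect.** Take 60% v 70% improved without surgery, with surgery in 20% v 10% of all children, every one then scoring A or C1: both arms reach 80%. But this needs 20/40 = 50% of unimproved control children and only 10/30 = 33% of unimproved autoinflation children to be operated on. With 50% in both arms, the 10-point difference becomes 10 × (1 − 0.5) = 5 points.

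It is also fair that a non-index ear may receive a tube because it developed effusion. Dropping such ears from outcome iv would delete real deterioration, so the remedy must keep them visible.

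Finally, the Introduction calls access to surgery extremely limited for many of these children, which would keep q small. It links the years-long waits to rural and remote areas, whereas this trial is urban and regional.

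**Conclusion.** The point holds for tympanometric outcomes i–iv. For outcome iv, the trace rule conflicts with the document's own condition for reading a flat trace as effusion, and this needs no assumption about surgery rates. For outcomes i–iii, the score of an operated child depends on the state of the tube, mainly at 6 months. The ear-level rule is written for 1 month, and its use at 3 and 6 months is the natural reading of item ii.

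The size is unknown. Under equal surgery shares among unimproved children, and with all operated children scoring A or C1, the difference moves towards no effect by the factor 1 − q: from an assumed 15 points to between 14.3 and 10.5 for q from 5% to 30%. If operated ears trace flat, the difference does not move.

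The 1-month primary outcome is largely protected from surgery by the entry exclusion, and the sample size stands. This is a correction to secondary outcomes, worth making before the 6-month data are analysed.

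**What to change.** In Outcomes, Secondary outcomes and in Statistical analyses, Secondary outcomes:

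1. Use the planned otoscopy and record review to place flat traces with a perforation or tube in their own category. Report them as a change in the ear, but do not label or count them as OME.
2. Keep the intention-to-treat (treatment-policy) result for the 3- and 6-month tympanometric outcomes, and say that this is the strategy.
3. Pre-specify a sensitivity analysis in which tube insertion or other middle-ear surgery between randomisation and the visit counts as not improved (child) or not resolved (ear), whatever the trace.
4. Report tube insertion and middle-ear surgery by arm.

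The otoscopy and the 6-month record review are already planned, so the cost is wording, one extra outcome category and one extra analysis. No clinical rule is changed.

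### Secondary outcome iv is named new OME but counts moves to C2 or C3, which the protocol says can neither diagnose nor exclude OME

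*Protocol article*

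**What the plan says.** All references are to the protocol article.

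- **Outcomes, Secondary outcomes, item iv** counts the "Proportion of tympanometric deterioration from a type A or C1 tympanogram to C2, C3, or B tympanogram in non-index ears" at 1, 3 and 6 months. Its parenthetical short name is "new OME by ear — unilateral subgroup".
- **Tympanometry box, under Diagnosis and incidence of otitis media with effusion**, treats A and C1 as showing no effusion. On type B it says: "A flat type B trace is diagnostic of middle ear effusion in the absence of pain and/or a bulging or perforated tympanic membrane". C2 and C3 traces "are considered equivocal and cannot be used to either diagnose or exclude OME".
- **Study population/eligibility criteria** rests OME at entry on type B: children "aged 3–16 years with unilateral or bilateral type B tympanograms are eligible for inclusion".
- **Outcomes, Primary outcome** uses the same composite for the other ear but calls it only deterioration: improvement must occur "without deterioration (type A or C1 to type C2, C3, or B tympanogram) in the contralateral ear".
- **Statistical analyses, Secondary outcomes** specifies a generalised linear model with log link for binary outcomes, so item iv will be summarised by a relative risk.

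**The concern.** Under the protocol's own diagnostic rule, an ear that moves from A or C1 to C2 or C3 has not been diagnosed with OME. Item iv nevertheless counts it under a name that says it has. In the list of secondary outcomes the parentheticals act as short names, and short names tend to reach table titles and abstracts.

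Item iv is the only listed outcome that isolates the initially unaffected ear. Elsewhere that ear enters only as a condition on child-level improvement. It is therefore where a reader would look to see whether autoinflation prevents or provokes effusion in a healthy ear. The article describes the device as designed to introduce air into the middle ear, so an effect on pressure traces that differs from the effect on effusion is plausible. A single mixed count cannot tell the two apart.

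**Working it through.** **1. Setting the sections side by side**

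| Place | Trace types | What they are taken to mean |
|---|---|---|
| Tympanometry box | B | diagnostic of effusion, with stated conditions |
| Tympanometry box | C2, C3 | equivocal in both directions |
| Eligibility | B | OME at entry |
| Primary outcome | A/C1 to C2, C3 or B | deterioration |
| Secondary outcome iv | A/C1 to C2, C3 or B | new OME |

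Only the last row treats C2 and C3 as OME. The 1-month rule under Treatment groups also places C2 and C3 alongside A and C1 ("Participants cease autoinflation at 1 month if they have bilateral type A, C1, C2, or C3 tympanograms"). That is noted only as another place where these traces are not handled as OME; no view is taken on the clinical rule.

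**2. The plan's own figures**

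The article gives no rate, relative risk or power for item iv, so there is no stated figure to reproduce for it. The stated sample size does reproduce: 35% against 50%, two-sided 5%, 80% power and pooled variance give 170 per group, 340 in total, and 340 / 0.85 = 400. Item iv plays no part in that calculation.

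**3. How the composite relates to new type B**

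Let pB and pC be the control proportions moving to type B and to C2/C3, and let RR_B and RR_C be the treatment effects on each.

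- Labelled control proportion = pB + pC, which is (pB + pC) / pB times the type B proportion.
- Labelled RR = (pB × RR_B + pC × RR_C) / (pB + pC).

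The labelled RR is a weighted average of the two component RRs. It equals RR_B only if pC = 0 or RR_C = RR_B.

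**4. Illustration**

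Every input here is an assumption. pB is set at 10%.

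| RR_B | pC | RR_C | Control | Treated | Labelled RR |
|---|---|---|---|---|---|
| 0.60 | 0% | – | 10% | 6% | 0.60 |
| 0.60 | 5% | 1.0 | 15% | 11% | 0.73 |
| 0.60 | 10% | 1.0 | 20% | 16% | 0.80 |
| 0.60 | 20% | 1.0 | 30% | 26% | 0.87 |
| 0.60 | 10% | 0.6 | 20% | 12% | 0.60 |
| 0.60 | 10% | 0.5 | 20% | 11% | 0.55 |
| 0.60 | 10% | 1.5 | 20% | 21% | 1.05 |
| 1.00 | 10% | 0.5 | 20% | 15% | 0.75 |
| 1.00 | 10% | 1.5 | 20% | 25% | 1.25 |

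For example, in the third row, (0.10 × 0.60 + 0.10 × 1.0) / 0.20 = 0.80. With pC from 5% to 20%, the labelled control proportion is 1.5 to 3.0 times the type B proportion. The RR moves towards 1 when C2/C3 changes are unaffected by treatment, stays put when both effects are equal, and can otherwise move either way.

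**The case against.** The strongest reply is that the operative text of item iv is explicit. It names the trace types counted and calls the event tympanometric deterioration, so the estimate would be right for what is defined and the problem is a short parenthetical. That stands. A reader might infer that the reported rate and relative risk are bound to be wrong, but the documents do not support this. The rate and RR of the defined composite would be correct, and even as an RR for new type B the figure is unchanged when treatment affects both components equally.

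A second reply is that type B alone is not the truth about effusion. This also stands: the box says C2 and C3 do not exclude OME. On the protocol's reading, the proportion with new effusion lies somewhere between the type B and composite proportions, so type B supplies the diagnosed figure and not the true one.

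Third, the composite has a purpose. It matches the contralateral condition in the primary outcome and shows how a unilateral child can fail on it. This is a good reason to keep it, but not to call it new OME.

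A reader might also infer that flat traces from acute otitis media or a perforated drum will be counted as new OME at follow-up. The article does not say so; it is silent. Video pneumatic otoscopy is listed as a data source, and ear pain and ear discharge are recorded as events of interest. How otoscopy qualifies a follow-up type B trace is detail that a condensed article may leave to the full protocol or analysis plan, so it forms no part of this point.

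**Conclusion.** The name given to item iv contradicts the protocol's own diagnostic criteria, and nothing in the article resolves this. Reported under that name, the proportion will exceed the type-B-diagnosed proportion if any non-index ear moves to C2 or C3, and its RR may mislead about new type B in either direction. That much follows from the definitions. The size and the direction of any difference in RR cannot be derived from the documents, and the illustrative figures rest wholly on assumed transition rates and effects.

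The reach is limited to one secondary outcome in the unilateral subgroup. The primary outcome, its analysis and the sample size are untouched. The change is still worth making before analysis, because it determines what the trial can say about new effusion in the initially unaffected ear.

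**What to change.** - Keep the composite, and rename it tympanometric deterioration in the non-index ear, in line with the primary outcome.
- Report A or C1 to type B separately at 1, 3 and 6 months, and reserve the name new OME for that row.
- Show A or C1 to C2 or C3 as its own category, on the same denominator, so that a reader can see which component drives the composite.

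The tympanograms are already collected at these visits, so the cost is a wording change and a few table rows. The downside is fewer events, and so a wider interval, for the type B row.
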